## Abstract

**Background:**

Non-thyroidal illness syndrome (NTIS) is a characteristic functional constellation of thyrotropic feedback control that frequently occurs in critically ill patients. Although this condition is associated with significantly increased morbidity and mortality, there is still controversy on whether NTIS is caused by artefacts, is a form of beneficial adaptation, or is a disorder requiring treatment. Trials investigating substitution therapy of NTIS revealed contradictory results. The comparison of heterogeneous patient cohorts may be the cause for those inconsistencies.

**Objectives:**

Primary objective of this study is the identification and differentiation of different functional states of thyrotropic feedback control in order to define relevant evaluation criteria for the prognosis of affected patients. Furthermore, we intend to assess the significance of an innovative physiological index approach (SPINA) in differential diagnosis between NTIS and latent (so-called "sub-clinical") thyrotoxicosis.

Secondary objective is observation of variables that quantify distinct components of NTIS in the context of independent predictors of evolution, survival or pathophysiological condition and influencing or disturbing factors like medication.

**Design:**

The **a**pproach to a **qua**ntitative **f**ollow-up **o**f **n**on-**t**hyroidal **i**llness **s**yndrome (AQUA FONTIS study) is designed as both a cross-sectional and prospective longitudinal observation trial in critically ill patients. Patients are observed in at least two evaluation points with consecutive assessments of thyroid status, physiological and clinical data in additional weekly observations up to discharge. A second part of the study investigates the neuropsychological impact of NTIS and medium-term outcomes.

The study design incorporates a two-module structure that covers a reduced protocol in form of an observation trial before patients give informed consent. Additional investigations are performed if and after patients agree in participation.

**Trial Registration:**

ClinicalTrials.gov NCT00591032

## Background

Non-thyroidal illness syndrome (NTIS or euthyroid sick syndrome) is a complex endocrine condition that may occur in critically ill patients. It is associated with significant deterioration of prognosis.

NTIS is characterised by three components that may occur single or in combination:central hypothyroidism (transient thyrotropic insufficiency), impaired protein binding of thyroid hormones and reduced formation of T3 with simultaneously increased conversion to rT3 (low-T3-syndrome) [1,2].

In 1973, characteristic alterations of thyroid metabolism have been first described in the starving organism [3,4]. Additional observations could reveal that these alterations are also common in critically ill patients where they form the correlate of endocrine dysregulation with increased morbidity and mortality [5-8].

However, explanation concepts for this complex constellation are different. Up to now, in essence five hypotheses are discussed in literature [2]:

1. All observed abnormalities are the result of test artefacts. In reality, the patients are euthyroid.

2. The changes in the levels of peripheral thyroid hormones mirror the effect of certain binding inhibitors that influence

A) laboratory results only or

B) also the transfer of thyroid hormones into the tissue of diseased persons and thus diminish binding of iodothyronines to T3 receptors.

3. Due to increased local deiodation, T3-levels are normal in the pituitary gland while they are low in the rest of the organism.

4. Levels of peripheral thyroid hormones are actually low so that affected patients are biochemically hypothyroid. However, this useful physiological function should not be manipulated.

5. NTIS is secondary or tertiary hypothyroidism. The resulting tissue hypothyroidism should be treated with appropriate substitution therapy [2].

Despite of intensive and long lasting research to many of its details NTIS is still poorly characterized in an integrative view. Additionally, a clinically usable classification is lacking.

Given the fact that patients with NTIS are faced with poor prognosis, several studies have been conducted in the past evaluating the question of possible treatment [2,7]. However, they did not yield unambiguous results. Some studies could show a benefit of substitution therapy with thyroid hormones, e.g. regarding the incidence of atrial fibrillation [2,7,9,10] and hemodynamic parameters [11,12] while others could not observe relevant differences in outcome between treated and untreated patients [13-15]. Several studies even described detrimental effects of substitution therapy ranging from increased risk of hyperthyroidism [16,17] over undesirably high protein catabolism [18] to severe side effects in patients with adrenal insufficiency that may be difficult to identify during critical illness [19]. Recently, a small trial investigating the effect of selenium substitution on the development of critically ill patients demonstrated improvements in prognosis, but, in spite of the known selenium-dependency of peripheral deiodinases, this outcome was not caused by a direct effect on thyroid homeostasis [20].

The problem of inconclusive and partly contradictory study results is aggravated by the fact that there is no consistent definition of NTIS that delimits this constellation from euthyroid state and that weighs the associated components regarding their relevance. Therefore, it may be assumed that the mentioned studies compared inhomogeneous patient groups.

An additional challenge affecting clinical practice is the fact that partial thyrotropic insufficiency in the course of NTIS can hardly be distinguished from latent ("subclinical") hyperthyroidism – although pathophysiology and therapeutic implications are opposed.

### Objectives of the AQUA FONTIS project

The AQUA FONTIS study (**a**pproach to a **qua**ntitative **f**ollow-up **o**f **n**on-**t**hyroidal **i**llness **s**yndrome) is primarily intended to develop a clear-cut definition and classification of NTIS (Table 1). Overall, this project is proposed to deliver a prognostic aid by providing a differentiated classification, to contribute to a standardised, rational and inexpensive diagnostic procedure in form of quantitative indices, and to lay the foundation for future therapeutic trials by identifying subgroups that may benefit from therapy.

**Table 1 T1:** Proposed "HPD" classification

**Facet**	**Possible values**
Hypothalamic-pituitary dysfunction or adaptation ("H")	H0: Normal TSH secretion, adequate to T4 level H1: Thyrotropic insufficiency
	
Impaired plasma protein binding ("P")	P0: Normal binding to plasma proteins P1: Normal binding with reduced levels of plasma proteins P2: reduced binding to proteins within normal levels P3: reduced binding and reduced protein levels
	
Reduced deiodation ("D")	D0: Normal deiodation D1: Reduced deiodation activity

Example: H1P0D1: Thyrotropic insufficiency with reduced deiodation and normal protein binding.

Outcome measure of this primary objective is the comparison of different decision criteria as presented in Table 2. These criteria are assessed with regard to the prognosis of the patients. Additionally, the significance of an innovative physiological index approach (SPINA) [21] is to be evaluated regarding its applicability for differential diagnosis between NTIS and latent thyrotoxicosis. It will therefore be evaluated in terms of sensitivity, specificity and likelihood ratios with ROC analysis.

**Table 2 T2:** Decision criteria

**Criterion**	**Definition**
Thyrotropic insufficiency	a) Reduced levels of both TSH and free T4. b) Thyrotroph T4 Sensitivity Index (TTSI) reduced below its reference interval.
	
Reduced plasma protein binding	a) Reduced relative ratios of bound and free hormone levels b) Reduced apparent dissociation constant of T3 at thyroxin binding globulin (K_30_)
	
Reduced deiodation	a) Reduced level for free T3 b) diminished T3/T4-ratio c) reduced sum activity of peripheral 5'-Dejodinase (G_D_^)

As secondary objective, we plan to observe variables that quantify distinct components of NTIS in the context of independent predictors of evolution, survival or pathophysiological condition as well as influencing or disturbing factors like medication or medical procedures. Outcome measures are correlations between quantitatively described components and external factors as well as their distributions in the context of dichotomic influencing factors.

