### Recruitment and criteria for inclusion and exclusion

This study recruits critically ill patients treated in one medical and two surgical intensive care units of the Bergmannsheil University hospitals for evaluation of integrative thyrotropic control and follow-up. Inclusion and exclusion criteria are presented in table 3. The diagnostic criteria are based on the ICD-10 system [22].

**Table 3 T3:** Inclusion and exclusion criteria of the AQUA FONTIS study

**Inclusion**	**Exclusion**
Severe illness requiring intensive care	Substituted hypothyroidism (E03.0, E03.1, E03.3 E03.9, E89.0) or substitution in case of thyroid carcinoma (C73)
	
Stay of at least 24 hours at the ICU	Hyperthyroidism treated with thyrostatic agents and exhibiting a TSH level not below the reference region (E05.0 E05.9, E06.2)
	
	Manifest AIDS disease (B24)
	
	Pregnancy

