### Decision criteria

Latent (so called "subclinical") thyrotoxicosis is defined as suppressed thyrotropin levels with free T4 levels being in their reference intervals and additional clinical evidence for tissue hyperthyroidism (suggestive history or Burch-Wartofsky point scale of more than 45 points [23]). Decision criteria to be evaluated are reproduced in Table 2.

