### Calculations

Thyrotroph T4 Sensitivity Index (TTSI) is calculated as

(1)$$TTSI=\frac{100[TSH][FT_{4}]}{l_{u}}$$

with *l*_*u *_being the upper limit of the reference interval for free T4 [24]. Theoretical secretion capacity of the thyroid gland (G_T_^) is computed with

(2)$${\hat{G}}_{T}=\frac{\beta_{T}(D_{T}+[TSH])(1+K_{41}[TBG]+K_{42}[TBPA])[FT_{4}]}{\alpha_{T}[TSH]},$$

where parameters are taken from Table 4[21].

**Table 4 T4:** Parameters for structure parameter inference [21]

**Symbol**	**Explanation**	**Value**
α_T_	Dilution factor for T4 (reciprocal of apparent volume of distribution)	0,1 l^-1^
β_T_	Clearance exponent for T4	1,1 * 10^-6 ^sec^-1^
D_T_	EC_50 _for TSH	2,75 mU/l
K_41_	Dissociation constant T4-TBG	2 * 10^10 ^l/mol
		
K_42_	Dissociation constant T4-TBPA	2 * 10^8 ^l/mol
		
α _31_	Dilution factor for T3	0,026 l^-1^
β _31_	Clearance exponent for T3	8 * 10^-6 ^sec^-1^
K_M1_	Dissociation constant of type-1-deiodinase	5 * 10^-7 ^mol/l
		
K_30_	Dissociation constant T3-TBG	2 * 10^9 ^l/mol

Sum activity of peripheral 5'-deiodinase (G_D_^) is defined with

(3)$${\hat{G}}_{D}=\frac{\beta_{31}(K_{M1}+[FT_{4}])(1+K_{30}[TBG])[FT_{3}]}{\alpha_{31}[FT_{4}]},$$

parameters are again from Table 4[21].

Apparent dissociation constant of T3 binding to TBG is obtained with

(4)$${\hat{K}}_{30}=\frac{\left[T_{3}]-[FT_{3}\right]}{\left[TBG][FT_{3}\right]}$$

from levels of iodothyronines and TBG.

Relative binding ratio is calculated with

(5)$$R_{B}=\frac{\frac{\left[T_{3}\right]}{l_{l,TT3}}}{\frac{\left[FT_{3}\right]}{l_{l,FT3}}}$$

where *l*_*l*, *TT*3 _denotes the lower limit of the reference interval for TT3 and *l*_*l*, *FT*3 _is the lower limit of the reference interval for FT3.

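### Criterion b for thyrotropic insufficiency (low TTSI) also captures thyrotoxicosis with clearly suppressed TSH, and no stated step separates the two before the prognosis comparison

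*Protocol article*

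**What the plan says.** Table 1 (Objectives of the AQUA FONTIS project) gives the hypothalamic-pituitary facet two values: "H0: Normal TSH secretion, adequate to T4 level H1: Thyrotropic insufficiency". Table 2 lists two candidate criteria for thyrotropic insufficiency. Criterion a is "Reduced levels of both TSH and free T4". Criterion b is "Thyrotroph T4 Sensitivity Index (TTSI) reduced below its reference interval".

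Equation (1) under Calculations defines TTSI as 100 × TSH × FT4 / l_u, with l_u "being the upper limit of the reference interval for free T4".

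The Decision criteria section defines latent thyrotoxicosis as "suppressed thyrotropin levels with free T4 levels being in their reference intervals and additional clinical evidence for tissue hyperthyroidism". That evidence is a suggestive history or a Burch-Wartofsky score above 45.

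The only exclusion in Table 3 that concerns hyperthyroidism is "Hyperthyroidism treated with thyrostatic agents and exhibiting a TSH level not below the reference region". The Background says that partial thyrotropic insufficiency in NTIS is hard to tell from latent hyperthyroidism, "although pathophysiology and therapeutic implications are opposed".

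Comparing the Table 2 criteria on prognosis is the outcome measure of the primary objective, and the Statistics section builds its main null hypothesis on it.

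**The concern.** TTSI is a product, so it falls in proportion to TSH whatever made TSH low. A pituitary that fails to respond and a pituitary correctly suppressed by excess thyroid hormone can both give a low value. Criterion a separates them, because it also requires low FT4. Criterion b does not.

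If thyrotoxic patients are in the cohort, criterion b puts them in H1 and criterion a does not. A difference in prognosis between the a and b groups could then partly reflect thyrotoxic patients rather than which criterion better identifies insufficiency. The article blames earlier conflicting results on inhomogeneous patient groups and hopes to find subgroups that may benefit from therapy. An H1 class of mixed composition works against both aims.

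**Working it through.** **Inputs from the article.** Equation (1); criteria a and b of Table 2; the definition of latent thyrotoxicosis; the exclusions in Table 3; the visit schedule in Table 5.

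**Inputs assumed.** The article gives no reference interval for TSH, FT4 or TTSI, and no numerical meaning for suppressed. I took a TSH lower limit of 0.3 to 0.5 mU/l, a TSH upper limit of 3.5 to 4.5 mU/l, and a ratio of lower to upper FT4 limit of 0.40 to 0.50.

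**Step 1: plausible lower limit of TTSI.** Two constructions were used.
- Both hormones at their lower limits: 100 × TSH lower limit × FT4 ratio. This runs from 100 × 0.3 × 0.40 = 12 to 100 × 0.5 × 0.50 = 25.
- The 2.5th percentile in a simulated healthy population (log-normal TSH, normal FT4, correlation 0 or −0.3): 18.6 to 38.8.

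The range carried forward is about 12 to 39.

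**Step 2: latent thyrotoxicosis.** FT4 is in range, so FT4/l_u ≤ 1 and TTSI ≤ 100 × TSH. Criterion b is then certain whenever 100 × TSH is below the TTSI limit. With the smallest assumed limit this means TSH below 12/100 = 0.12 mU/l.

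**Step 3: values of TTSI.**

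| TSH (mU/l) | FT4 = l_u | 2 × l_u | 3 × l_u | 5 × l_u |
|---|---|---|---|---|
| 0.01 | 1 | 2 | 3 | 5 |
| 0.05 | 5 | 10 | 15 | 25 |
| 0.1 | 10 | 20 | 30 | 50 |
| 0.2 | 20 | 40 | 60 | 100 |
| 0.39 | 39 | 78 | 117 | 195 |

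- TSH 0.1 or less with FT4 in range: TTSI at most 10, below every assumed limit. Criterion b is met.
- TSH 0.01 with FT4 up to 5 × l_u: TTSI at most 5. Criterion b is met.
- TSH 0.1 with raised FT4: criterion b stops being met once FT4 reaches about 1.2 to 3.9 × l_u, depending on the assumed limit.
- TSH 0.2 with FT4 = l_u: TTSI is 20, above or below the limit depending on the assumption.
- TSH 0.39 with FT4 = l_u: TTSI is 39. With a TSH lower limit of 0.4, the TTSI limit is 16 to 31. Criterion b is not met.

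**Step 4: criterion a.** It needs reduced FT4. Latent thyrotoxicosis has FT4 in range by definition, and thyrotoxicosis with raised FT4 fails too. Neither meets criterion a.

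**Step 5: who is in the cohort.** The Table 3 exclusion needs both thyrostatic treatment and TSH not below reference. Untreated hyperthyroidism, and treated hyperthyroidism with low TSH, stay eligible. The Discussion adds that existing thyroid disease may be missed.

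**Step 6: effect on the comparison.** Let a fraction p of the H1 group under b be thyrotoxic, with mortality m_T, and let the rest have mortality m_I. The group then shows (1 − p) × m_I + p × m_T, a shift of p × (m_T − m_I) from the insufficiency value. The article gives none of these quantities, so the shift cannot be put in figures.

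**The case against.** The strongest reply is that Table 2 lists candidates. Table 1 is headed as a proposal, and the study compares a with b because they classify patients differently, so poor specificity of b would be a study result. This stands in part: nobody is finally classed as H1 by criterion b alone. But the comparison is the primary result, and on prognosis alone it cannot show whether b differs from a through better detection of insufficiency or through added thyrotoxic patients.

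Second, keeping thyrotoxic patients serves the stated aim of separating NTIS from latent thyrotoxicosis, and the authors name the overlap. This stands: their eligibility is not an error. It does not follow that they belong unmarked in the H1 prognosis group. SPINA is evaluated as a separate question and is not stated as a step before criterion b.

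Third, the order of classification could be left to a fuller document. Here, however, the criterion and the exclusion are both stated, and as stated they give the overlap.

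Two stronger readings are tempting. A reader might infer that every patient with suppressed TSH meets criterion b. The calculations do not bear this out: TSH just below its limit with high-normal FT4, or TSH of 0.1 with clearly raised FT4, can escape it, and the article gives no TTSI interval to settle the cut. A reader might also infer that the two groups in the ROC analysis overlap. The article does not say that criterion b defines the NTIS group, so this is only conditional.

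**Conclusion.** The point holds for clearly suppressed TSH. Criterion b, as written, counts such thyrotoxicosis as thyrotropic insufficiency, criterion a does not, and the article states no step that separates the two before the facet-H prognosis tests.

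The boundary of about 0.1 mU/l with FT4 in range, or about 0.01 mU/l with FT4 up to 5 × l_u, rests on the assumed reference limits, but holds across the whole assumed range. Between that boundary and the lower TSH limit, the result depends on FT4 and on a TTSI interval that is not given.

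The direction and size of any distortion are unknown, because neither the prevalence of thyrotoxicosis nor its prognosis in this cohort is stated. This should be corrected, but it does not invalidate the design.

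**What to change.** Before applying criterion b, flag probable thyrotoxicosis for the analysis, using only data scheduled for all patients in the ICU phase:
- low TSH with raised FT4 at EP 1.1; or
- suppressed TSH with FT4 in range at EP 1.1, and a suggestive history at EP 1.0.

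State the TSH cut-off for suppressed and the TTSI reference interval alongside the flag. Report the facet-H prognosis tests and the comparison of a with b both with and without flagged patients.

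Do not use the Burch-Wartofsky score to remove patients from mortality analyses. Table 5 schedules it only at EP 2.0 and 2.1, so only patients who reach the ward and consent can have it. Removal on that basis would take out survivors more readily than ICU deaths.

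If criterion b is used to define the NTIS group for the ROC analysis, make that group and the latent thyrotoxicosis group mutually exclusive.

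The cost is one classification step on data already scheduled and a second run of the same analyses. The unflagged analysis will have somewhat fewer patients. Latent cases whose history was missed will stay in the b group, so the separation is incomplete and the report should say so.

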## Methods

The AQUA FONTIS study is designed as both a cross-sectional and prospective longitudinal observation trial (Figure 1).

**Figure 1 F1:**
[figure not shown]
**Flowchart of the AQUA-FONTIS study with its two intertwined modules.** See text and table 5 for detailed information.

### Recruitment and criteria for inclusion and exclusion

This study recruits critically ill patients treated in one medical and two surgical intensive care units of the Bergmannsheil University hospitals for evaluation of integrative thyrotropic control and follow-up. Inclusion and exclusion criteria are presented in table 3. The diagnostic criteria are based on the ICD-10 system [22].

**Table 3 T3:** Inclusion and exclusion criteria of the AQUA FONTIS study

**Inclusion**	**Exclusion**
Severe illness requiring intensive care	Substituted hypothyroidism (E03.0, E03.1, E03.3 E03.9, E89.0) or substitution in case of thyroid carcinoma (C73)
	
Stay of at least 24 hours at the ICU	Hyperthyroidism treated with thyrostatic agents and exhibiting a TSH level not below the reference region (E05.0 E05.9, E06.2)
	
	Manifest AIDS disease (B24)
	
	Pregnancy

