### Follow-up and Evaluation Points

Patients are subjected to at least one evaluation point. Critically ill persons that are newly admitted to an ICU are screened in the first EP (1.0) for fulfilment of the inclusion and exclusion criteria from Table 3 and entered in the database (see below). The second EP (1.1) is performed after 24 hours; only those eligible patients that are still under intensive care will be included in the study and subsequently prospectively observed. On the occasion of this and the subsequent EPs (after 72 hours for EP 1.2 and weekly in the further course of the study), severity scores like SAPS II and APACHE II as well as physiological parameters and data regarding pharmacological therapy or medical interventions are surveyed (Table 5). Additionally, laboratory investigations that are part of routine diagnostics (e.g. TSH, FT4, total T3, inflammation parameters, total protein etc.) are complemented by those parameters that are collected for the study (total T4, free T3 and antibodies against iodothyronines as well as thyroid tissue). As all required specimens are taken in the course of routine diagnostic procedures, additional assays, but no additional blood samples are necessary.

**Table 5 T5:** Schedule of evaluation points

	EP 1.0	EP 1.1	EP 1.2	EP 1.3	EP 1.999
	Screening	After 24 hours	After 72 hours	Weekly	After discharge

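### Thyroid hormone substitution is excluded only under listed ICD-10 codes, and recorded intake outside them can shift the competing Table 2 criteria in different directions

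*Protocol article*

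**What the plan says.** Under Recruitment and criteria for inclusion and exclusion, Table 3 excludes "Substituted hypothyroidism (E03.0, E03.1, E03.3 E03.9, E89.0) or substitution in case of thyroid carcinoma (C73"). The same section states: "The diagnostic criteria are based on the ICD-10 system". The only other exclusion tied to a thyroid drug is "Hyperthyroidism treated with thyrostatic agents and exhibiting a TSH level not below the reference region", which does not cover thyroid hormone.

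Medication is collected. At EP 1.1 and later, "data regarding pharmacological therapy or medical interventions are surveyed", and Table 5 marks medication at all five evaluation points of the first part, including EP 1.0. Its stated analytic use is under the secondary objective, which looks at "influencing or disturbing factors like medication or medical procedures".

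The Statistics section tests the Table 2 criteria against prognosis. It names no restriction or adjustment for thyroid hormone exposure. The only stops of observation that the article states after inclusion are readmission to the ICU and withdrawal of consent.

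**The concern.** Table 3 accepts that hormone intake makes a patient unsuitable, because intake blurs what the thyroid axis does by itself. That reason does not depend on the diagnosis code, but the exclusion does. Intake under an unlisted diagnosis, or with none coded, passes as written. Goitre without hypothyroidism is one illustration; it is not named in the article.

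The stake is the primary outcome measure, which compares alternative decision criteria for the same component of NTIS by their relation to prognosis. If recorded drug exposure moves one criterion towards positive, leaves another unchanged and moves a third towards negative, part of the apparent difference between criteria reflects the drug and not the illness.

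**Working it through.** The article gives no figure on this point to reproduce. The check puts hormone patterns into its own formulas.

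**From the article.**
- Equation 1: TTSI = 100 × TSH × FT4 / l_u.
- Equation 3: G_D = β31 (K_M1 + FT4)(1 + K30 × TBG) FT3 / (α31 × FT4).
- Table 4 constants: β31 = 8×10⁻⁶ /s, α31 = 0.026 /l, K_M1 = 5×10⁻⁷ mol/l, K30 = 2×10⁹ l/mol.
- Table 2 criteria. Thyrotropic insufficiency: (a) TSH and free T4 both low, or (b) TTSI below its range. Reduced deiodination: (a) low free T3, (b) "diminished T3/T4-ratio", or (c) reduced G_D.

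**Assumed, not in the documents.** l_u = 23 pmol/l, TBG = 300 nmol/l, baseline TSH 1.5 mU/l, FT4 15 pmol/l, FT3 5 pmol/l, and the three exposure patterns below. The T3/T4 ratio is taken as FT3/FT4.

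**Step 1, form of G_D.** K_M1 (5×10⁻⁷ mol/l) far exceeds FT4 (order 10⁻¹¹ mol/l), so (K_M1 + FT4)/FT4 is close to K_M1/FT4, and G_D is nearly proportional to FT3/FT4. A 25% rise in FT4 at unchanged FT3 gives 1/1.25 = 0.80, a fall of 20%.

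**Step 2, patterns.**

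| Pattern | TSH | FT4 | FT3 | TTSI | G_D (nmol/s) | FT3/FT4 |
|---|---|---|---|---|---|---|
| Baseline | 1.5 | 15 | 5 | 97.8 | 30.8 | 0.333 |
| Suppressive T4 (FT4 +30%) | 0.1 | 19.5 | 5 | 8.5 | 23.7 (−23%) | 0.256 |
| Replacement T4 (FT4 +15%, FT3 −5%) | 1.5 | 17.25 | 4.75 | 112.5 | 25.5 (−17%) | 0.275 |
| T3 (FT4 −45%, FT3 +40%) | 0.1 | 8.25 | 7 | 3.6 | 78.5 (+155%) | 0.848 |

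For example, suppressive T4 gives TTSI = 100 × 0.1 × 19.5/23 = 8.5, and T3 gives G_D = 30.8 × 1.40/0.55, about 78.5.

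**Step 3, reading against Table 2.**
- Suppressive T4 moves TTSI, T3/T4 and G_D towards positive. It does not meet low TSH with low free T4, because free T4 rises, and it does not lower free T3.
- Replacement T4 does not lower TTSI. It lowers the ratio and G_D.
- T3 lowers TTSI, and meets low TSH with low free T4 if free T4 falls below its range. It raises the ratio and G_D, so reduced deiodination is masked.

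**Step 4, how much could depend on it.** Let q be the exposed share and p the true prevalence of a positive criterion. If every exposed patient scored positive on that criterion, exposed patients would form q/(q + (1−q)p) of all positives. Both q and p are assumed.

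| q (of 650) | p = 10% | p = 20% | p = 30% |
|---|---|---|---|
| 1% (about 7) | 9.2% | 4.8% | 3.3% |
| 3% (about 20) | 23.6% | 13.4% | 9.3% |
| 5% (about 33) | 34.5% | 20.8% | 14.9% |

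For a given q and p these are ceilings, since Step 3 shows that no criterion is moved to positive by all three patterns.

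**The case against.** Several points on the other side are sound.

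- *Intake is in the criterion.* A reader might infer that Table 3 ignores intake and looks only at diagnoses. It does not: substitution is the operative word, limited by codes.
- *Medication is not ignored.* It is recorded throughout and studied under the secondary objective. The Discussion also concedes that existing thyroid disease or previous medication may be missed. That concession concerns unknown use, however. Use that is known and recorded still enters the main test.
- *The code list may be wider than it looks.* E03.3 and E03.9 are printed without a separator, as are E05.0 and E05.9, so a range dash may have been lost in text extraction. If so, further hypothyroidism codes are covered. The rule would still be bounded by a list.
- *Treatment started in the ICU is not documented.* The Background notes that "Some studies could show a benefit of substitution therapy with thyroid hormones", and thyroid values are among the "laboratory investigations that are part of routine diagnostics (e.g. TSH, FT4, total T3"). A reader might infer that these units start hormone in sicker patients, so that treatment by indication mimics a prognostic effect. The article reports conflicting published trials and does not say that these units give thyroid hormone.
- *Handling after inclusion may stand elsewhere.* A full protocol or SAP could hold such a rule, so its absence from the article is not itself the fault. The eligibility rule is stated here and can be judged here.
- *G_T is beside the point.* Equation 2 is also affected by supplied T4, but G_T is not a Table 2 criterion.

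**Conclusion.** The point holds in a limited form. The exclusion covers substitution only under listed codes, so recorded intake for other reasons reaches the main comparison, where the article states no restriction for it. The direction of the distortion follows from equations 1 and 3 once a hormone pattern is assumed, and it differs by hormone and by criterion.

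A reader might go further and infer that users are generally scored as having thyrotropic insufficiency or reduced deiodination. The documents do not support that: T4 works against low TSH with low free T4, replacement T4 need not lower TTSI, and T3 hides reduced deiodination. Nor is a specific drug-made share of positives supported. The documents give no share of exposed patients, so the 3.3% to 34.5% range above only shows how strongly the answer depends on assumed inputs. A shift in an index also need not cross its reference limit. The size is unknown; the defect is that the competing criteria are exposed to it unequally.

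**What to change.** Define the exclusion for the main analysis as any recorded thyroid hormone intake before admission, whatever the diagnosis code. Apply it to the 470 patients already included as well, using the medication entry that Table 5 schedules at EP 1.0. First confirm that this entry, or the history taken at the same point, captures intake before admission.

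If thyroid hormone or thyrostatic drugs start after inclusion, assign the Table 2 criteria from evaluation points before the first recorded dose and keep the patient's outcome. Report the analysis with and without exposed patients and points, and state how many there were.

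The cost is one reworded restriction and one flag on data already scheduled. Some patients or later evaluation points, probably few, leave the main analysis. Because the restriction is applied retrospectively to enrolled patients, the parallel analysis without it should be shown. Unrecorded earlier use remains a limitation, as the Discussion says. No treatment rule changes.
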